# Protocol for a prospective, multicenter, parallel-group, open-label randomized controlled trial comparing standard care with Closed lOoP In chiLdren and yOuth with Type 1 diabetes and high-risk glycemic control: the CO-PILOT trial

**DOI:** 10.1007/s40200-024-01397-4

**Published:** 2024-03-07

**Keywords:** Type 1 diabetes, Advanced hybrid closed loop, Automated insulin delivery, Artificial pancreas, Children and youth, Glycemic control

## Abstract

**Purpose:**

Advanced hybrid closed loop (AHCL) systems have the potential to improve glycemia and reduce burden for people with type 1 diabetes (T1D). Children and youth, who are at particular risk for out-of-target glycemia, may have the most to gain from AHCL. However, no randomized controlled trial (RCT) specifically targeting this age group with very high HbA_1c_ has previously been attempted. Therefore, the CO-PILOT trial (Closed lOoP In chiLdren and yOuth with Type 1 diabetes and high-risk glycemic control) aims to evaluate the efficacy and safety of AHCL in this group.

**Methods:**

A prospective, multicenter, parallel-group, open-label RCT, comparing MiniMed™ 780G AHCL to standard care (multiple daily injections or continuous subcutaneous insulin infusion). Eighty participants aged 7–25 years with T1D, a current HbA_1c_ ≥ 8.5% (69 mmol/mol), and naïve to automated insulin delivery will be randomly allocated to AHCL or control (standard care) for 13 weeks. The primary outcome is change in HbA_1c_ between baseline and 13 weeks. Secondary outcomes include standard continuous glucose monitor glycemic metrics, psychosocial factors, sleep, platform performance, safety, and user experience. This RCT will be followed by a continuation phase where the control arm crosses over to AHCL and all participants use AHCL for a further 39 weeks to assess longer term outcomes.

**Conclusion:**

This study will evaluate the efficacy and safety of AHCL in this population and has the potential to demonstrate that AHCL is the gold standard for children and youth with T1D experiencing out-of-target glucose control and considerable diabetes burden.

**Trial registration:**

This trial was prospectively registered with the Australian New Zealand Clinical Trials Registry on 14 November 2022 (ACTRN12622001454763) and the World Health Organization International Clinical Trials Registry Platform (Universal Trial Number U1111-1284-8452).

**Supplementary Information:**

The online version contains supplementary material available at 10.1007/s40200-024-01397-4.

## Introduction

Maintaining healthy glycemic control is challenging for people with type 1 diabetes (T1D). This is particularly so for children, and adolescents and young adults (henceforth referred to as “youth”) as their attempts to manage glucose levels to target can be limited by risk of hypoglycemia, fear of hypoglycemia, their own or their caregivers’ burden of care, and less treatment adherence e.g. in form of missed bolus insulin delivery and less frequent self-monitoring of blood glucose [1–3]. Accordingly, less than a third of children and youth with T1D achieve glycemic targets known to reduce the risk of developing diabetes complications and improve life expectancy [1, 4]. More efficacious and burden reducing therapies are clearly required to improve outcomes.

### Advanced hybrid closed loop

Advanced hybrid closed loop (AHCL), sometimes referred to as artificial pancreas or automated insulin delivery (AID), is currently the most advanced commercial insulin delivery technology for T1D, having evolved from early sensor augmented pump (SAP) therapy, and then hybrid closed loop [5, 6]. AHCL integrates real-time continuous glucose monitoring (rtCGM), continuous subcutaneous insulin infusion (CSII), and a computer algorithm to partially automate insulin delivery [7]. Several commercial AHCL systems are currently available and are defined by their ability to not only modulate basal insulin delivery but also provide varying degrees of automated boluses to correct high glucose levels [6]. Evidence from randomized controlled trials (RCTs) supports the potential of AHCL to safely improve glycemic outcomes, including improving HbA_1c_ while reducing hypoglycemia [8–14]. These data have now led to AHCL being the gold standard for insulin therapy for most people with T1D as recommended in current guidelines [15, 16]. However, these trials have often not been inclusive of those of non-European ethnicity nor varying socioeconomic status, and often excluded people with suboptimal glycemic control (particularly those with HbA_1c_ > 10% [86 mmol/mol]).

These individuals may in fact have the most to gain from automating insulin delivery and reducing diabetes burden. Current early data suggests this with a recent prospective 3-month single arm study among youth with out-of-target glycemia (average baseline HbA_1c_: 10.5% [91.2 mmol/mol]), highlighting very large HbA_1c_ improvements of on average 2.9% points (31.5 mmol/mol) following rapid onboarding of AHCL, with sustained improvements after 12 months of AHCL [17, 18]. Similar data are suggested for other AHCL systems, but have not been tested at extremes of elevated HbA_1c_ [10]. In addition, children and youth with out-of-target glucose control and from diverse backgrounds do appear interested in wearable diabetes technology and have engaged with past trials [19–22].

Equitably improving diabetes care for children and youth burdened by the requirements of diabetes care and the ability to achieve recommended glycemic targets is of paramount importance, given the full lifetimes of diabetes ahead of them, as well as the future substantial risk of long-term complications and mortality if their diabetes remains out of target [23, 24]. In New Zealand, only 2.3% of children and adolescents use AID, limited by absence of funding for CGM systems and restricted access to publicly funded insulin pump therapy, which disproportionally disadvantage youth and those of non-European ethnicity [25, 26]. The impact of out-of-target glycemia on sleep in youth is of further concern, given that suboptimal glycemic control has been demonstrated to impair various aspects of healthy sleep [27, 28], which in turn has been associated with impaired diabetes management and general health and wellbeing [29, 30]. The CO-PILOT trial is the first RCT comparing AHCL with standard diabetes care (multiple daily injections [MDI] and CSII) to test our hypothesis that AHCL will improve glucose control and reduce burden of care in children and youth with suboptimal glycemia naïve to AHCL and struggling to achieve recommended glycemic targets with traditional insulin therapies.

## Methods

### Study design

The CO-PILOT trial is comprised of a prospective, multicenter, parallel-group, open-label randomized controlled superiority trial evaluating the effectiveness and safety of AHCL compared to usual care over 13 weeks in 80 children and youth with T1D and suboptimal glycemic control (HbA_1c_ ≥ 8.5% [69 mmol/mol]), as shown in Fig. 1. A 2-week baseline data collection phase will precede the 13-week RCT, followed by a 39-week study continuation where control participants cross over to AHCL and all participants use AHCL until study conclusion. Total duration of participant involvement will be 54 weeks. The trial has been approved by the Southern Health and Disability Ethics Committee (Wellington, New Zealand; Ethics reference: 2022 FULL 13,508) and Māori (indigenous New Zealanders) Research Consultation Committees in each region.

**Fig. 1 Fig1:**
[figure not shown]
CO-PILOT study design. A total of 80 participants will be randomized; other sample sizes remain blank (n=) until trial completion

### Sample size

Using a standard deviation of 23 mmol/mol and a within-person correlation of 0.6 [17, 31], a sample size of 64 (32 participants per group) would be required to determine a conservative difference in change in HbA_1c_ of 15 mmol/mol with 90% power to the alpha of 0.05 level (single arm data suggests > 15mmol/mol achievable in this population [17]). To account for 20% loss of data and participant attrition (inflated compared to other trials to allow for potentially greater loss of data due to the high-risk population), a sample size of 80 will be recruited (40 participants per group).

### Study population and recruitment

A total of 80 participants will be recruited at four diabetes centers across New Zealand (Dunedin, Christchurch, Wellington, and Auckland public hospitals) on a first-come first-serve basis. Participants will be patients receiving standard care through Te Whatu Ora– Health New Zealand diabetes services, identified by their usual endocrinology/diabetology team during routine clinical visits, invited to participate and provided with preliminary study information. Eligibility will be confirmed during screening visits. Inclusion criteria: aged 7 to 25 years inclusive; diagnosed with T1D as per American Diabetes Association classification [32] for ≥ 1 year; current HbA_1c_ ≥ 8.5% (69 mmol/mol); total daily dose (TDD) of insulin ≥ 8 units/day. Key exclusion criteria are: previous use of closed loop technology; pregnancy; use of medication indicative of diabetes complications (ACE inhibitors and statins permitted), systemic glucocorticoids, metformin, sodium-glucose cotransporter − 2 inhibitors, or glucagon-like peptide-1 receptor agonists; history of severe medical or psychiatric co-morbidities; any concomitant condition that would interfere with the study conduct or pose an unacceptable risk to participants. For diabetic retinopathy and other visual impairment, until future data on moderate to severe retinopathy is available, potential participants will be eligible if they meet the following criteria (based on internationally accepted grading criteria [33]): (A) Nil or minimal retinopathy– no restriction on study entry; (B) if Grade 1/mild retinopathy and HbA1c < 10% (86 mmol/mol)– no restriction to study entry; (C) if Grade 1/mild retinopathy and HbA_1c_ ≥ 10% (≥ 86 mmol/mol)– diabetic retinopathy screening to be performed during the study pre-screening phase. If subject remains at Grade 1/mild retinopathy and frequency of screening is deemed ≥ 1 year (indicating less clinical concern), inclusion criteria are met. If subject has progressed to moderate (Grade 2) or severe (Grade 3) diabetic retinopathy, to be excluded; (D) any diabetic retinopathy classed at or beyond moderate (Grade 2) or severe (Grade 3) non-proliferative retinopathy excluded; (E) history of severe visual impairment excluded. ISPAD guidelines [34] for diabetic retinopathy screening will be followed while in study care. These are: Screening from age 11 years with 2 to 5 years diabetes duration. Subsequent monitoring frequency 2- to 3-yearly (or as locally recommended/available).

### Study procedures

At screening/enrolment (Visit 1), prior to the start of any study-related procedures, written informed consent/assent will be obtained from participants and, if applicable, their legal guardians (for participants aged 7 to 15 years, and inclusive). Subsequently, demographic and anthropometric data, date of T1D diagnosis, current insulin therapy, prior CGM use, and co-morbidities will be recorded. Episodes of diabetic ketoacidosis (DKA) and severe hypoglycemia (defined as coma or convulsion requiring assistance from others) within the previous 12 months will be collected. Female participants of child-bearing potential will perform a urine pregnancy test. To confirm eligibility, HbA_1c_ will be measured by a calibrated point-of-care device. All participants will commence 2-week blinded CGM (Guardian™ Sensor 3 and Link 3 transmitter, Medtronic, San Francisco, CA) for continuous collection of baseline glycemic data. Participants will be instructed to perform self-monitoring blood glucose (SMBG) calibration at least 3 times daily during this phase (Contour Next Link 2.4 m, Medtronic). Questionnaires for participant-reported psychosocial and sleep outcomes will be administered, and habitual sleep patterns will be recorded using actigraphy prior to randomization.

### Meal announcement procedures

Participants will complete a dietitian-generated carbohydrate counting assessment tool to guide method of AHCL meal announcement (Suppl. Information S1) [35]. Based on assessment scores, participants will be instructed to announce AHCL meals by using either a flexible method of precise carbohydrate counting (flex method) or a preset of three fixed carbohydrate amounts for meals (fix method). These preset amounts for snacks, regular meals, and large meals will be personalized based on a 3-day food diary completed by participants.

Providing these two options for carbohydrate counting ensures knowledge of carbohydrate counting is not a potential barrier for using AHCL, as well as tests the philosophy that carbohydrate counting is required to obtain an insulin pump as part of this clinical trial. In support of this approach, recently published data from study investigators suggest that simplified fixed carbohydrate meal announcements are an effective alternative for AHCL users who struggle with precise carbohydrate counting [35].

### Randomization

Prior to study commencement, a randomization sequence for a 1:1 allocation with permuted blocks of random size, stratified by pre-randomization HbA_1c_ (8.5–11.2%, or ≥ 11.3% [69–99 mmol/mol, or ≥ 100 mmol/mol]) and age (aged 7–15 years, or aged 16–25 years) will be generated by a biostatistician using Stata 17.0 (StataCorp, College Station, TX) and imported into the Research Electronic Data Capture (REDCap) randomization module [36]. The REDCap project will subsequently be moved into production, rendering the randomization sequence inaccessible and preserving allocation concealment. Participants will be randomly allocated to the intervention arm (commence AHCL) or control arm (continue standard care) following baseline data collection using the randomization module. Participants and study staff will not be blinded to this intervention assignment.

### Study groups

#### Intervention arm

Participants allocated to intervention will undergo our previously published 72-hour rapid onboarding protocol (Wheeler-Petrovski initiation protocol) [17]. In brief, participants will be trained in the use of the MiniMed™ 780G AHCL insulin pump with Guardian™ 4 sensor and Guardian™ Link 4 transmitter (Medtronic, San Francisco, CA), and Accu-Chek™ Guide Link blood glucose meter (Roche, Basel, Switzerland) and commence sensor augmented pump therapy with predictive low glucose management (SAP + PLGM). Key system settings will be as follows: total daily basal dose reduced by 20% of participant’s previous dose if MDI, and identical if CSII; active insulin time (AIT) of 3.0 h; insulin-to-carbohydrate ratio (ICR) calculated using the formula 500/TDD and insulin sensitivity factor (ISF) in mmol/L calculated using the formula 100/TDD (1800/TDD for mg/dL), or participant’s established CSII ratios will be used. Suspend before low limit will be set at 58 mg/dL (3.2 mmol/L), with alert on low activated, and suspend before low alert and high glucose alert deactivated. Bolus increment will be set at 0.025 units. After using the system in SAP + PLGM mode for 72 h, the SmartGuard™ feature will be activated with the following settings: Algorithm target set at 100 mg/dL (5.5 mmol/L), or, if concerns of frequent hypoglycemia, 110 mg/dL (6.1 mmol/L) or 120 mg/dL (6.7 mmol/L) at investigator’s discretion; automated corrections on; AIT of 2.5 h. At investigator’s discretion, over time the above settings can be adjusted as required, and AIT will be adjusted to 2.0 h within the first weeks of the RCT as able. Participants will use the AHCL system continuously for 13 weeks.

The SmartGuard™ feature incorporates a model-based adaptive algorithm with proportional-integral-derivative insulin-feedback module, which automatically adjusts basal insulin delivery every 5 min to achieve glucose levels determined by a target sensor glucose (SG) value. The system can furthermore deliver an automated correction bolus up to every 5 min as required based on SG values and is designed to provide optimal results at a target of 100 mg/dL (5.5 mmol/L) and AIT of 2.0 h in most people [37]. For exercise or other high-activity occasions, a temporary SG target of 150 mg/dL (8.3 mmol/L) can be selected, during which automated bolus corrections are disabled.

Participants’ AHCL system data will be uploaded to CareLink™ Clinical Therapy Management Software (Medtronic, San Francisco, CA) using either the MiniMed™ Clinical App, or alternatively in case of app access issues a Bluetooth-enabled USB adapter (Blue Adapter, LG Innotek, Seoul, South Korea). Research staff will review data uploads remotely daily while participants are using SAP + PLGM therapy. Subsequently, remote data reviews and participant contact including setting adjustments, if required, will be daily for one week following SmartGuard™ initiation, then weekly for 4 weeks, then monthly until the end of the RCT. Setting adjustments will be verified by research staff during remote data reviews. Data flow in this study is depicted in Fig. 2.

**Fig. 2 Fig2:**
[figure not shown]
Data flow in the CO-PILOT study

#### Control arm

Control participants will continue their usual diabetes therapy (MDI or CSII [without automated insulin delivery]) throughout the 13-week RCT, and will receive remote contact from study staff at the same frequencies as described for the intervention group, including insulin dosing and glycemic data reviews, and management interventions as needed. Participants will repeat blinded CGM for continuous collection of end-of-study glycemic data during the final 2 weeks of the RCT. CGM use in the control group will be documented and reported, but no restrictions on CGM use are in place (other than those restricting AHCL/AID).

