### Glycemic metrics

CGM data will be collected from CareLink™ software and analyzed according to standardized CGM metrics for clinical care [41]. Time in range (TIR) will be recorded as the percentage of time with sensor glucose levels in the range 70–180 mg/dL (3.9–10.0 mmol/L); time in tight range (TITR) as the percentage of time with sensor glucose levels in the range 70–140 mg/dL (3.9–7.8 mmol/L); hypoglycemia as the percentage of time with sensor glucose levels below 70 mg/dL (3.9 mmol/L) and below 54 mg/dL (3.0 mmol/L); hyperglycemia as the percentage of time with sensor glucose levels above 180 mg/dL (10.0 mmol/L) and above 250 mg/dL (13.9 mmol/L). TIR will also be differentiated by day (0600–2359 h) and night (0000–0559 h).

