### Statistical analysis

Statistical analyses will be performed using the up-to-date version of specialist statistical software (R, SAS, or Stata), and results will be reported in line with the CONSORT statement. The biostatistician will be blinded to intervention assignment and will use non-informative group codes until all analyses are completed. Appropriate descriptive statistics will be presented for all variables, including means and standard deviations for continuous normally distributed variables and counts and percentages for categorical variables. The primary analysis will follow the intention-to-treat principle, with participants analyzed as per randomization allocation. A secondary per-protocol analysis will also be conducted where only those participants in the intervention group using SmartGuard™ for at least 70% of the time will be included. An alpha of 0.05 will be considered statistically significant. Mixed effects regression models will be used to estimate mean differences in outcomes, with 95% confidence intervals and p-values between groups. Models will be adjusted for baseline and stratification variables. A random effect for site will be included. There will be no adjustment for multiple comparisons. Residuals of all models will be plotted to assess whether homoscedasticity assumptions are met. If necessary, outcome variables may be log-transformed or quantile regressions undertaken.

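### Week-13 CGM comes from a study sensor in controls but from the treatment system's own sensor in the AHCL arm, so missing glucose data in that arm are tied to not using the treatment

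*Protocol article*

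**What the plan says.** At baseline the two arms are measured alike: under Study procedures, everyone wears the same blinded Guardian Sensor 3 for 2 weeks. At week 13 they are not. Under Control arm: "Participants will repeat blinded CGM for continuous collection of end-of-study glycemic data during the final 2 weeks of the RCT". No matching sentence appears under Intervention arm. There, "participants will be trained in the use of the MiniMed™ 780G AHCL insulin pump with Guardian™ 4 sensor and Guardian™ Link 4 transmitter", and "Participants’ AHCL system data will be uploaded to CareLink™ Clinical Therapy Management Software". The Glycemic metrics section names CareLink as the source of the CGM outcomes. The Discussion confirms the split, since it places the limitation of the blinded sensor at baseline and in the control group only.

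Outcome measures and Table 1 schedule glycemic metrics at 13 weeks, and the Outcome measures text puts the secondary outcomes in the last 2 weeks of the RCT. Under Statistical analysis the primary analysis is by intention to treat, "with participants analyzed as per randomization allocation". A separate per-protocol analysis restricts the AHCL arm to those with at least 70% SmartGuard use. Under Sample size, 20% is allowed for data loss and attrition, on the ground of "potentially greater loss of data due to the high-risk population".

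**The concern.** In the control arm, wearing the outcome sensor is separate from taking insulin: someone who neglects treatment can still wear the study sensor for 2 weeks. In the AHCL arm the outcome sensor is a component of the treatment, and automation cannot run without it. Hours without sensor data are therefore hours off automation, and a participant who has given the system up has no described route to a week-13 CGM value.

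Analysis by allocation needs those participants and hours in the AHCL mean. If they are absent, time in range, time above range and time below range compare AHCL while worn with standard care however it was followed. Baseline adjustment and a mixed model with a single post-baseline CGM value do not repair this, because both rely on missingness being ignorable given what was observed, and here it depends on treatment use. The problem would remain if both arms used the same sensor model.

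**Working it through.** **The plan's own figure.** The article gives no sample size or expected value for time in range. Its only calculation is for HbA1c, and it reproduces. Baseline-adjusted SD = 23 × √(1 − 0.6²) = 18.4 mmol/mol. With a difference of 15 mmol/mol, two-sided alpha 0.05 and power 90%, this needs 32 per group, 64 in all (power 0.903 at 32 per group), and 64 / (1 − 0.20) = 80. So the 20% is a whole-trial allowance for HbA1c. It is not a forecast of missing CGM in the AHCL arm and serves below only as an upper value.

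**Assumed inputs** (none is in the document):
- control time in range 30%
- AHCL time in range 55-65% on the system and 25-35% off it
- share q of the AHCL arm without week-13 sensor data 5-20% (2 to 8 of 40)
- sensor wear w among the rest 70-90%, with a worn-minus-unworn gap g of 10-30 points
- share h of control readings lost above 400 mg/dL 2-15%, with no such loss in the AHCL arm.

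**1. Participants without data.** Observed AHCL mean = on-system value; mean by allocation = (1 − q) × on + q × off. Excess = q × (on − off).
- Smallest: 0.05 × (55 − 35) = 1.0 point.
- Largest: 0.20 × (65 − 25) = 8.0 points.
- At q = 10%: 0.10 × 20 = 2.0 to 0.10 × 40 = 4.0 points.

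**2. Unworn hours in participants with some data.** Excess = (1 − w) × g.
- Smallest: 0.10 × 10 = 1.0 point.
- Largest: 0.30 × 30 = 9.0 points.

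**3. The opposing bias named in the Discussion.** Lost readings are all above range, so observed control time in range = 30 / (1 − h).
- h = 2%: 30 / 0.98 = 30.6, shrinking the difference by 0.6 points.
- h = 15%: 30 / 0.85 = 35.3, shrinking it by 5.3 points.

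**4. Net of steps 1 and 3.** From 8.0 − 0.6 = +7.4 to 1.0 − 5.3 = −4.3 points. The sign is not determined.

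**The case against.** Several objections have force.

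- **Inference from silence.** Nowhere does the article say that AHCL discontinuers go unmeasured. Table 1 lists glycemic metrics at 13 weeks without exception, and the data-flow figure and full protocol are not at hand. This stands as a limit on certainty about discontinuers. It does not touch the arm-specific source, which the Control arm section and the Discussion both state.
- **Sensor wear is not SmartGuard use.** The system can run with the sensor worn and automation off, and Platform performance records the two separately. This stands: the 70% SmartGuard threshold is no evidence of missing CGM. The link runs one way, since time without the sensor is always time without automation.
- **Controls lose data too.** They may decline to wear the blinded sensor, and if the baseline calibration instruction is repeated, the least engaged may lose most. So missing CGM is not confined to the AHCL arm. Specific to that arm is that the outcome sensor is also part of the treatment.
- **Direction.** A reader might infer that the reported benefit will be overstated. The document does not support that: the loss of high control readings flatters control time in range, and its size is unknown. An unquantified opposing bias does not cancel this one, but it does prevent a claim about the net result.
- **Remedy.** AHCL sensor wear is already to be reported. Adding a sensor because of post-randomization behaviour, judged by unblinded staff, could be selective, and someone who has abandoned one sensor may refuse another. These points argue for a pre-stated cut-off and a sensitivity analysis, not for leaving the gap.

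**Conclusion.** The point holds for the secondary CGM outcomes. The week-13 glucose source differs by arm, and in the AHCL arm missing data are tied to treatment non-use, so the comparison by allocation drifts towards a while-worn comparison. Taken alone, the mechanism favours AHCL, by 1 to 8 points of time in range if 5-20% of the arm lacks data, or 1 to 9 points from unworn hours. Both ranges rest wholly on assumed values. The net bias in the CGM comparison cannot be signed from the document. The HbA1c primary outcome and its sample size are unaffected. It is worth changing because the remedy is cheap and uses a sensor that every participant has already worn at baseline.

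**What to change.** Extend the week-13 blinded CGM sentence beyond the control arm. Any AHCL-arm participant still in the study who, at the start of the final 2 weeks, has stopped AHCL or falls below a pre-stated wear cut-off for the Guardian 4 sensor is offered the same blinded CGM as controls, and those data are analyzed under the allocated arm. Report by arm the percentage of the 2-week window covered by CGM and the number with no CGM outcome. Add a sensitivity analysis in which missing AHCL-arm CGM takes control-like or baseline values. If the full protocol already measures discontinuers this way, the article needs only a sentence saying so.

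Cost: one protocol sentence, one analysis and a few sensors of a type already in use. A few AHCL participants would be measured with the control-type sensor, with extra wear and calibration burden. That sensor may also lose their highest readings, so the correction could be partial. Participants who have left the study remain unmeasured, which is why the sensitivity analysis is still needed.
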